#### Selection and random assignment of camps for the trial

Due to the density of geographically proximal camps (see Fig. 2), we used a three step, probability based sampling method that reduced the possibility of contamination effects to randomly select 60 eligible camps in to the trial: (1) field staff familiar with the physical geography of wards and camps assigned geographically proximal camps to groups containing between 1–6 camps on ArcGIS generated maps; (2) probability proportionate to size with minimal replacement sampling of groups was conducted using SAS Survey Select Procedure; (3) simple random selection of camps within groups selected was completed. By using minimal replacement, groups containing greater numbers of camps with high membership numbers could be selected more than once. In such an instance, the number of times a group was selected equaled the number of camps selected randomly from that group. The 60 randomly selected camps were first randomized into two sets of 30 camps. Multiple camps selected from within the same geographically proximally group were assigned to the same set. Treatment condition of these two sets was then randomly, and transparently, assigned at a CAB meeting following completion of baseline data collection. At the CAB meeting, the two sets were assigned numbers one and two. Papers with these numbers were then put in separate but identical balloons, and three other papers that stated “try again” in three other identical baloons. The CAB decided that the first number to be selected would be assigned to the intervention condition. One CAB member was selected to be the one to randomly pick and pop the balloons until a number was found.

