### Study assessments

Study assessments are conducted at baseline, 12-months post-intervention launch and at 30-months post-intervention. Behavioral surveys are collected at each assessment, and biological samples are collected at baseline and 30-month post-intervention only. Prior to the first assessment participants are asked for consent to participate in the study, which the participant provides by signing a consent form and writing their initials next to the assessments (behavioral, biological) to which they agree to participate. Participants must re-assent to participate in future behavioral assessments and consent to participate in biological assessment if not done at baseline. Behavioral surveys are conducted in field offices located in the study wards through computer-assisted personal interviews (CAPI) using tablet devices. Each interview is expected to take approximately 60–90 min to complete. Sixteen local interviewers, trained in human ethics, confidentiality, interviewing techniques, data collection methods, and use of CAPI devices, collect all behavioral data. To collect biological specimens, blood and urine samples are drawn from participants immediately after the behavioral survey is completed. To assess baseline prevalence of sexually transmitted infections (STIs), a subsample of 50 % of men that report ever having sex on their baseline survey are asked to provide a blood and urine specimen for HIV and STI tests. At the 30-month assessment, all men are asked to provide biological samples. Participants are refunded the equivalent of $3 for transport.

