### Measures

The primary endpoints to assess intervention impact are STI incidence and IPV perpetration. To assess STI incidence, we are using Qiagen Artus CT with in-house PCR to detect CT, Trichomonas vaginalis Real-TM test to detect TV, and 16 s rDNA PCR to detect NG. For the follow-up testing at 30 months we are using Multiplex PCR to detect CT and NG. Study participants who are identified with NG, CT, or TV are offered free treatment by a study clinician at the study site according to the standard of care in Tanzania specifically NG (Ceftriaxone), CT (Doxycycline), TV (Metronidazole). IPV perpetration is assessed using an adapted version of the World Health Organization violence against women instrument [63]. This tool measures psychological, physical, and sexual IPV perpetration. Participants are asked whether they have perpetrated any of 13 behaviorally specific violent acts, including 4 psychological acts, 4 physical acts and 3 sexually violent acts, against a current or former sexual partner. For those who say yes to ever having perpetrated a specific act of violence, they are asked to report how many times they perpetrated that act in the last 12 months. Response options included never, once, 2–3 times, 4–10 times, and more than 10 times. The responses to the frequency of physical and sexual IPV perpetration within the last 12 months are dichotomized such that a 0 represents no sexual/physical IPV perpetration and a 1 represents at least 1 act of sexual or physical IPV perpetration within the last 12 months. We are measuring gender norms with the gender-equitable men’s scale [36], as well as hope [64], future orientation [65], and perceived social support as mediators of the intervention’s effects. We are measuring camp-level social cohesion using five items adapted from a measure of social cohesion developed by Sampson, Raudenbush & Earls [66]. For example, participants are asked how strongly they agree with statements like “people in my camp are willing to help each other” and “the members of my camp share the same values.” In addition, we are collecting data on all social ties within each camp at multiple waves of data collection. We are using these complete network data to assess whether our intervention is mediated through the transformation of social network structures (e.g. structural cohesion [67]). Finally, we are also looking at HIV risk behaviors as secondary endpoints including unprotected sex, sexual partner concurrency, alcohol and other substance use.

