### Peer Health Leader component

The second component of the intervention targets peer leaders within camps, called camp health leaders (CHL), and trains them as health promoters for behavior change. This intervention component builds on the fact that it is possible to identify peer nominated leaders within the camps who are respected and trusted by their peers. We use the following steps to implement this component: *(1) Nomination of leaders:* Based on recommendations of previous studies [71] that have used peer opinion leaders to promote health behavior change in networks we aim to recruit 20 % of all camp members as CHLs. To identify CHLs we hold meetings with camp members in each camp. Prior to a nomination, members are asked to describe attributes of a leader. Research staff note these attributes and supplement the list with pre-determined qualities wanted in CHLs (e.g. someone who could be trusted with personal matters, someone whom you admire). At the conclusion of this discussion each camp member confidentially nominates up to 3 leaders in their camps with the qualities documented. Votes are tallied by the research coordinator. The top 20 % of camp members receiving the most votes in each camp are approached and asked if they are interested in participating in the camp health leader training. *(2) Training:* Peer leaders participate in an initial one-week training and two, single day booster training sessions held two and five months later. The trainings are facilitated by the site-PI and the Project Coordinator who are both master’s trained psychologists with expertise in training for counseling in this context. The training provides the leaders with knowledge to address myths and misconceptions related to HIV transmission and prevention, condoms, violence and multiple sexual partnerships. A major component of the training is building skills in effective communication for social influence. Through role playing and demonstrations, leaders learn how to engage their peers in conversations about sensitive topics, how to identify and address barriers to practicing safe sex, how to counter negative viewpoints, how to use ‘I’ statements when talking with their peers about behavior, how to be better listeners, and how to model positive behavior choices for their peers. The training module on gender-based violence includes several interactive activities that are designed to help the peer leaders clarify their own attitudes and values related to gender, violence and power and to help the leaders understand how violence affects women’s health and well-being. Additional booster training sessions are held bi-annually with the CHLs to review information covered in the initial training, and discuss success and challenges that the health leaders faced in implementing the strategies among their peers. CHLs receive a modest allowance (TZS 5,000, equivalent to USD 2.44) for the training days to cover costs associated with transportation to get to and from the training venue. *(3) Implementation of the communication and social influence strategies:* Once the CHL leaders are trained, they are asked to implement the strategies they learned among peers in the camps. This includes incorporating the material they learned in the training into naturally occurring conversations that they are having with members of their camp. *(4) Monitoring CHL conversations*: CHL are required to keep a weekly diary documenting the number of HIV and GBV specific conversations they have had with other camp members. We established a goal with the CHL of 5 conversations per week within the camp, to try to monitor dosage of conversations against this goal. These diaries are collected from CHLs and entered into an Access spreadsheet in Tanzania and synced weekly to a web-based server. Aggregated data and pre-configured statistics are accessed through a master database in the U.S. Graphs of the conversations by camp are created and viewed bi-monthly to identify CHLs who are achieving and those who are not achieving our target dosage goals.

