The study also has limitations. While the camps are generally stable networks of men, it’s possible that men’s engagement in camps may vary over time, and camp membership may shift over time, making it challenging to retain men in the trial. Second, as with all cluster-randomized trials, there is the potential for contamination, and particularly in our case since we are working in a densely population urban setting. We were careful to group contiguous camps to minimize contamination across camps that are most proximal, however, it is still possible given the dense urban setting, that camp members in camps assigned to different conditions may share information. To measure the magnitude of contamination, intervention exposure is measured in both intervention and control camps during the 12-month and 30-month survey by asking participants to identify the other camps that they visited and assessing the frequency with which they visit these camps. We also ask participants whether they talk to individuals in those other camps about HIV or gender-based violence during the intervention period. Finally, it is possible that by working with existing social networks, characteristics of these networks such as how cohesive they are may influence how camp members do or do not engage in the intervention activities. As part of our secondary analysis, we examine how network characteristics influence the study outcomes across the camps. Our documentation of the network characteristics and their influence on study implementation and outcomes will contribute valuable information to the scientific understanding of how to design and implement social network interventions.

Effective approaches to engage men in HIV and IPV prevention are needed in low resource, high prevalence settings like Tanzania. If we determine that this approach is effective, we will examine how to adapt and scale up this approach to other urban, sub-Saharan African settings.

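### The primary IPV outcome is self-reported to an interviewer in an openly allocated trial with violence messaging in one arm only, so greater under-reporting in that arm could produce or inflate a protective effect

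*Protocol article*

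**What the plan says.** **Outcome.** IPV perpetration is one of two primary endpoints (protocol article, Measures). It is the man's own report: "Participants are asked whether they have perpetrated any of 13 behaviorally specific violent acts". For each act he admits to ever committing, "they are asked to report how many times they perpetrated that act in the last 12 months". The result is dichotomised so that "a 1 represents at least 1 act of sexual or physical IPV perpetration within the last 12 months".

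**Mode.** Under Study assessments: "Behavioral surveys are conducted in field offices located in the study wards through computer-assisted personal interviews (CAPI) using tablet devices". Sixteen trained interviewers "collect all behavioral data". No self-completed section is described.

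**Allocation.** "Treatment condition of these two sets was then randomly, and transparently, assigned at a CAB meeting following completion of baseline data collection" (Selection and random assignment of camps). The community advisory board includes leaders of study camps (Research ethics section).

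**Intervention.** About 20% of members in each intervention camp are to be trained as health leaders. "The training module on gender-based violence includes several interactive activities that are designed to help the peer leaders clarify their own attitudes" (Peer Health Leader component). The leaders then raise HIV and gender-based violence in conversation with other members, with a goal of five conversations a week recorded in a diary. Control camps receive the intervention later.

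**Analysis and limitations.** Data analysis compares reported past-year IPV across arms at 30 months. The limitations in the Discussion cover retention and shifting membership, contamination, and network characteristics. Arm-dependent reporting is not among them.

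**The concern.** A man who has committed one or more acts becomes a non-case if he denies them all. Men know whether their camp received loans and peer leaders. Over two years the intervention camps hear, through those leaders, a message about violence that comes from the same study whose interviewer later asks about it. Control men do not. This gives intervention men a study-created reason to offer the approved answer, whether or not their behaviour changed.

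Survey weights, the clustering adjustment and a larger sample do nothing about such a difference. The STI endpoint is a laboratory result and is not open to this bias, but it does not verify reports of violence. Gender-role attitudes, a hypothesised mediator, come from the same survey, so socially desirable answering could move attitudes and reported violence together. At stake is whether a lower odds ratio for IPV can be read as less violence rather than less disclosure.

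**Working it through.** **Inputs from Sample size determination.** Design odds ratio 0.65 for IPV; 80% power, two-sided α = 0.05; 890 sexually active men (999 men in all) in 60 camps at 30 months; behavioural ICC 0.032; design effects 1.4 to 2.3.

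**Assumptions.** Control-arm prevalence is not stated, so 20%, 30% and 40% are used. The nearest figure, in the Background, is 23.8% of women in the city reporting physical violence in the last 12 months, which concerns a different population and leaves out sexual violence. The extra share denying, *f*, is also an assumption.

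**Step 1: the plan's own figures.** 60 × 26.4 × 0.80 × 0.80 = 1,014 against 999, and 1,014 × 0.90 = 912 against 890, both within 3%. The power at 0.65 cannot be reproduced uniquely without the control prevalence. The bias does not depend on it; 0.65 serves only as a yardstick.

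**Step 2: odds ratio produced by reporting alone.** Let *p0* be the reported prevalence in the control arm. Under-reporting common to both arms is already inside *p0*, so *f* is only the excess in the intervention arm. With no true effect, the intervention arm reports q = p0(1 − f), and

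OR = [q/(1 − q)] / [p0/(1 − p0)].

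Example, p0 = 0.30 and f = 0.10: q = 0.27, and (0.27/0.73)/(0.30/0.70) = 0.370/0.429 = 0.86.

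**Step 3: excess denial that reproduces 0.65.** p1 = 0.65·o/(1 + 0.65·o) with o = p0/(1 − p0), and f = 1 − p1/p0.

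| p0 | OR, f = 10% | OR, f = 20% | p1 at OR 0.65 | f needed for 0.65 |
|---|---|---|---|---|
| 20% | 0.88 | 0.76 | 14.0% | 30% |
| 30% | 0.86 | 0.74 | 21.8% | 27% |
| 40% | 0.84 | 0.71 | 30.2% | 24% |

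**Step 4: chance of a falsely significant result.** With 890/60 = 14.8 men per camp, the design effect is 1 + 13.8 × 0.032 = 1.44, so n = 445/1.44 = 309 effective men per arm. Let d = p0 − q and p̄ = (p0 + q)/2, with se0 = √[2p̄(1 − p̄)/n] and se1 = √{[p0(1 − p0) + q(1 − q)]/n}. The two-sided rejection probability is Φ[(d − 1.96·se0)/se1] + Φ[(−d − 1.96·se0)/se1].

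| p0 | f = 10%, DE 1.44 | f = 20%, DE 1.44 | f = 10%, DE 2.3 | f = 20%, DE 2.3 |
|---|---|---|---|---|
| 20% | 10% | 25% | 8% | 18% |
| 30% | 13% | 39% | 10% | 26% |
| 40% | 18% | 55% | 13% | 37% |

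The nominal rate is 5%.

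**Step 5: the opposite sign.** If the intervention made men 10% more likely to disclose, q = 1.1·p0 gives odds ratios of (0.22/0.78)/0.25 = 1.13 at 20% and (0.44/0.56)/0.667 = 1.18 at 40%. The bias would then mask benefit.

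**The case against.** **Direction.** A reader might infer that the bias can run only towards protection. The documents do not support that. Leaders are trained to open conversations on sensitive subjects and to understand how violence affects women, which could raise recognition or disclosure. Asking about specific acts limits the recognition route, so under-reporting remains the more likely direction, but it is not proven. This objection stands as a limit on the claim.

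**Strength of exposure.** The violence module goes directly only to the health leaders; other members meet it in everyday conversation with them. Loans and business training come from a separate microfinance organisation. The intervention runs two years and endline is at 30 months, so the primary interview falls about six months after it ends. All of this weakens the pressure without removing the difference between arms.

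**Interviewers and item order.** A reader might infer that interviewers know the arm, helped deliver the programme, or ask about exposure before violence. The Discussion says only that "intervention exposure is measured in both intervention and control camps during the 12-month and 30-month survey"; it gives no order. No section gives interviewers a delivery role: health-leader training is by the site principal investigator and project coordinator, and repayments are taken by loan officers. A condensed article can leave masking and questionnaire layout to the full protocol, so its silence is not an error.

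**Size.** Excess denial of 24% to 30% is a lot, and 10% moves the odds ratio only to 0.84 to 0.88. That is fair. Yet 10% already raises the false-positive rate above 5% in every row of Step 4, and partial bias can inflate a real effect.

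**Remedy.** The documents hold no evidence that self-completion removes arm-dependent denial. It takes away the spoken disclosure to study staff; it does not guarantee candour. That is why a sensitivity analysis is needed as well.

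**Conclusion.** The point holds as a threat to the interpretation of one primary endpoint, and something should be done about it. The article itself fixes self-report, interviewer collection, open allocation and one-sided messaging, and neither its analysis section nor its limitations deals with differential reporting. With no true effect and an assumed control prevalence of 20% to 40%, 10% excess denial gives an odds ratio of 0.88 to 0.84; 30% to 24% excess denial would be needed to reproduce the whole design effect. The actual degree of differential reporting is unknown.

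It would be too strong to conclude that a favourable IPV result could never be told apart from reporting bias. A large observed effect would need implausibly large differential denial to explain it, which is what the sensitivity analysis below would show.

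**What to change.** 1. **Mode.** At the 30-month survey, in both arms, have participants answer the IPV items privately on the existing tablets by audio self-interview in Swahili. Cost: reprogramming and recording one module, and an ethics amendment. The change of mode makes within-person change from the baseline and 12-month surveys harder to interpret, but the primary between-arm comparison at 30 months keeps one mode in both arms.
2. **Sensitivity analysis.** Prespecify a tipping-point analysis. For a grid of *f*, replace the observed intervention prevalence by that prevalence divided by (1 − f) and recompute the odds ratio. Report the *f* at which the upper 95% limit reaches 1 and the *f* at which the estimate reaches 1. Include negative *f* for greater disclosure. Cost: analysis time only.
3. **Limitations.** Add arm-dependent reporting to those in the Discussion.
4. **Confirm against the full protocol.** Check whether interviewers are masked to arm and separate from delivery, and whether the IPV items precede the exposure and contamination questions. If so, say so in the report.

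If the 30-month survey has already started, items 2 and 3 can still be done in full.

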### Sample size determination

The choice of 60 camps randomized into two groups is based upon evidence generated in our previous study and likely incidence estimates available from published studies with similar populations in Tanzania and other countries in Africa [10, 68]. We estimated average camp sizes of 26.4 men and expected to successfully enroll approximately 80 % of these men into our trial at baseline. 90 % of the men were expected to be sexually active at baseline. Any STI incidence (NG, CT, or TV) was used as the primary outcome measure and sexual and/or physical IPV perpetration was used as the primary behavioral outcome measures. Based upon our previous study we computed camp intraclass correlation (ICC) estimates between 0.00 and 0.01 for sexually transmitted diseases and 0.032 for behavioral measures. Given anticipated average camp sizes and ICC estimates we inflated sample size estimates assuming simple random sampling with design effects ranging from 1.4 to 2.3. All sample estimates assumed an attrition of 20 %. Given a sample size of 890 sexually active males and 999 total males in 60 camps at our 30-month assessment, we will have 80 % power (2-sided, α = 0.05) to detect protective effects of the intervention (OR) of .57 for STI incidence and .65 for perpetration of sexual or physical IPV among sexually active men. Statistical power to detect mediation is expected to be high based on the simulation results of Fritz and MacKinnon where a total sample size of 539 was sufficient for .80 power to detect the most conservative simulated mediation effect.

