### Data analysis

For our primary outcome analysis, we compare odds ratios for STI incidence and IPV perpetration in the past 12 months, across arms at 30 months for both behavioral and STI outcomes using SAS SURVEYLOGISTIC version 9.4 [69] to adjust for correlation due to clustering within camps and incorporate both the complex nature of sample selection and weighting. Controls for covariates will be introduced where necessary. In the event that program effects are identified, we will assess the degree to which hope, future orientation, and structural characteristics of the networks mediate the impact of the intervention on STI and IPV. Indirect (mediated) effects of the intervention will be calculated using Mplus and assessed for significance using construction of Monte Carlo confidence intervals [70].

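### The primary STI endpoint is named incidence, but the comparison that is planned and powered on 890 men measures 30-month point prevalence

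*Protocol article*

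**What the plan says.** The Measures section of the protocol article states: "The primary endpoints to assess intervention impact are STI incidence and IPV perpetration". The abstract, the primary hypothesis, the sample size section and the data analysis section all use incidence for the same endpoint, a positive result for NG, CT or TV.

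The sampling schedule is in Study assessments: "biological samples are collected at baseline and 30-month post-intervention only". At baseline, a 50% subsample of "men that report ever having sex on their baseline survey are asked to provide a blood and urine specimen for HIV and STI tests". The sentence that sets this up opens with the words "To assess baseline prevalence of sexually transmitted infections (STIs", so the stated purpose is to describe prevalence, not to establish a group known to be uninfected. At the end, "At the 30-month assessment, all men are asked to provide biological samples".

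Under Data analysis, "we compare odds ratios for STI incidence and IPV perpetration in the past 12 months, across arms at 30 months". No restriction to men with a negative baseline test is given. The power statement rests on "a sample size of 890 sexually active males and 999 total males in 60 camps at our 30-month assessment" and gives 80% power (two-sided 5%) for an odds ratio of 0.57 on STI incidence. The control-arm risk is not stated. The section says that the sample size draws on expected incidence figures from published studies.

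**The concern.** Incidence needs men known to be uninfected at the start, and a way of recording new infections. Here at least half of the men who have ever had sex have no baseline result, and nobody is tested between baseline and 30 months. A positive 30-month test in an untested man cannot be classed as new. A negative test in any man can hide an infection that was acquired and then cleared or treated.

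Two things are at stake. The first is the claim. A lower 30-month positivity in the intervention arm is a difference in prevalence, whereas the primary hypothesis is about incidence. The second is power. The article joins the word incidence to a sample size that only a prevalence analysis can use. Whichever reading is adopted, the stated 80% may not apply: one reading loses half the men, and the other may have a lower event rate than the incidence figures assumed.

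**Working it through.** **Inputs from Sample size determination.** 60 camps; 26.4 men per camp; 80% enrolled; 20% attrition; 90% sexually active; STI intraclass correlation 0.00 to 0.01; stated design effects 1.4 to 2.3; 80% power, two-sided 5%, odds ratio 0.57. From Study assessments: 50% of men who report ever having sex are asked for a baseline specimen.

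**The plan's sample size.** 60 × 26.4 × 0.80 × 0.80 = 1,014 men at 30 months, and × 0.90 = 912 sexually active. The plan has 999 and 890, so its figures reproduce within 3%. No allowance for missing baseline tests enters them.

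**Men who could support an incidence analysis.** 0.5 × 890 = 445 at most, if tested and untested men are retained equally. Excluding baseline positives at an assumed prevalence of 5% or 10% leaves 423 or 400.

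**Power formula.** With control risk p1, p2 has odds 0.57 × p1/(1 − p1). With p̄ the mean of the two and n = N/(2 × design effect) per arm:

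power = Φ{ [ |p1 − p2| − 1.96 √(2p̄(1 − p̄)/n) ] / √([p1(1 − p1) + p2(1 − p2)]/n) }

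Because p1 is not given, I set it to the value that makes the plan's 80% true at N = 890, so that any loss is measured against the plan's own figure. For example, with design effect 1.0, p1 = 16.5% and p2 = 10.1% give 80% with n = 445 per arm and 50.7% with n = 222.5 per arm.

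**Design effects.** With 890/60 = 14.83 men per camp, an intraclass correlation of 0.01 gives 1 + 13.83 × 0.01 = 1.14. A design effect of 1.4 corresponds to 0.4/13.83 = 0.029. Halving the men per camp to 7.42 lowers these to 1 + 6.42 × 0.01 = 1.06 and 1 + 6.42 × 0.029 = 1.19. I stop at 1.4 because at 2.3 no control risk gives 80% for an odds ratio of 0.57 on 890 men (the maximum is about 79%).

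| Design effect, 890 men | Control risk giving 80% | Design effect, 445 men | Power, 445 men | Detectable OR, 445 men | Power, 400 men |
|---|---|---|---|---|---|
| 1.0 | 16.5% | 1.0 | 50.7% | 0.43 | 46.6% |
| 1.14 | 19.1% | 1.06 | 53.4% | 0.45 | 49.5% |
| 1.4 | 24.4% | 1.19 | 57.5% | 0.47 | 53.9% |

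If the design effect stays at 1.4 in the half sample, the last row becomes 50.7%, 0.43 and 46.6%.

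**Prevalence reading, all 890 men.** At an assumed control positivity of 10%, p2 is 6.0% and power is 60.5%, 55.1% and 46.9% for design effects 1.0, 1.14 and 1.4.

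**Why the two quantities differ.** As an illustration, assume that all men start negative, acquisition is 0.10 per year, mean duration is 0.5 year (clearance rate 2 per year) and follow-up is 2.5 years. Cumulative incidence is 1 − exp(−0.25) = 22%. Point prevalence at the end is (0.10/2.10) × (1 − exp(−2.10 × 2.5)) = 4.7%. The single test then finds about a fifth of the men who were ever infected. The documents give neither rate nor duration.

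**The case against.** The strongest reply is that this is a label, not a broken design. All men in both arms are asked for a specimen at 30 months, and both arms have the same assays then, so the comparison in Data analysis is a valid randomised contrast. New positivity can also be derived among baseline-negative men. Both points stand. A reader might infer that incidence cannot be measured at all; that goes too far, since it is true of the full 890 but not of the tested half. Even there, one later test misses infections acquired and cleared in between.

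It can also be said that carry-over is small. Baseline ends two months before launch, so an old infection must last about 32 months. Under exponential clearance with an assumed mean duration of 0.5 or 1 year, 0.5% or 7% persist; at 2 years, 26%. If infections are short, most 30-month positives are new. That is fair, and missed infections are then the main limitation. The result is still a prevalence.

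Three further inferences are tempting and should not be drawn. One is that the intervention would lower positivity by increasing treatment seeking: the listed training content does not mention STI testing or treatment seeking. Another is that the change of CT and NG assay biases the primary comparison: it matters only for change within a man. The third is a further loss from refused specimens: no refusal rate is given, and men may consent later.

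Finally, the missing control risk and the rule for classing a case as incident may be in the full protocol or the SAP, so their absence is no fault here. But no analysis plan can supply baseline results for men who were never tested.

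**Conclusion.** The point holds as a mismatch between the named endpoint and what is measured, and it should be corrected because the endpoint is primary. On the 890 men used for power, the planned comparison is of 30-month point prevalence. It compares the arms validly but does not by itself support the hypothesis of lower incidence.

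If incidence is meant literally, power for an odds ratio of 0.57 is 51–58% with all 445 baseline-tested men and 47–54% with 400. The detectable odds ratio moves from 0.57 to about 0.43–0.47 before baseline positives are excluded. These figures assume the control risk that gives 80% at 890 men, design effects of 1.0 to 1.4 and equal retention. If prevalence is meant, the 80% needs a one-visit control positivity of about 16% to 24%. At an assumed 10% it is 47–61%, so inputs taken from incidence studies may overstate power. The documents do not show which inputs were used, so they do not establish that power is overstated.

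**What to change.** Define the primary biological endpoint as prevalence of any NG, CT or TV at the 30-month test among men tested, and use that term in the abstract, hypothesis, measures, sample size and analysis text. Make new infection among men who tested negative at baseline a secondary analysis, and note there that the CT and NG assays differ between the two visits. Restate the STI power for a 30-month prevalence on the same denominator as the analysis. Settle this before 30-month results are seen, so that the choice between the two analysis sets cannot follow the data.

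The cost is a narrower claim and possibly a less favourable power figure. No additional tests or participants are required.
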